## Abstract

**Background:** More than half of the people with dementia live in lower-middle income countries (LMIC), yet we lack research and evidence-based knowledge to guide health promotion and prevention strategies for cognitive decline. In the Philippines, the prevalence of mild cognitive impairment (MCI) and cardiovascular risk factors among older persons are high, making this population at high risk for developing dementia. This protocol describes a cluster randomized controlled trial that aims to investigate the efficacy of a multicomponent intervention to maintain cognitive performance among high-risk population.

**Methods:** This is a cluster-randomized, two-arm, single-blind trial of a multicomponent intervention that combines dance called INDAK (Improving Neurocognition through Dance and Kinesthetics), nutrition counseling, and vascular risk management. The intervention arm will receive 12 months (1-h, twice per week) of INDAK and every 3 months of nutrition counseling and intensive vascular risk management and monitoring. The control group will receive the usual vascular care advice and referral. A total of 605 (20–25 clusters per arm) community-dwelling Filipino older adults aged ≥ 60 years old with MCI will participate in the study and will be assessed at baseline, 6th- and 12th-month follow-up. The primary outcome is cognitive performance assessed by the Alzheimer's Disease Assessment Scale—Cognitive (ADAS-Cog), Mnemonic Similarity Tasks (MST), and executive function composite (EFC). Secondary outcomes are functional connectivity assessed through brain imaging, and measures of behavioral, functional level, and quality of life.

**Discussion:** The study aims to provide scientific evidence on a public health intervention that is contextualized in a community setting to reduce dementia risk among older adults with MCI. This model can be an ecological, low-cost, and effective program, thereby conducive to widespread implementation in the Philippines as well as in other low-resource settings with similar public health challenges. The pilot phase was underway with eight villages (clusters), but temporarily interrupted by the pandemic. The full study is anticipated to start after community restrictions are eased.

## Introduction

The Filipino aging population comprised about 7% of the country's total population in 2015 and is projected to increase by 11% in 2025 and 16% in 2045 (1). Like many other lower middle-income countries (LMIC), the Philippines is not only experiencing demographic aging but also undergoing epidemiological transition due to increased unhealthy diets, sedentary lifestyles, and poor healthcare leading to dramatic increase in dementia epidemic and its associated risks (2–4). In a population-based cohort study of Filipino older adults, aged ≥ 60 years, we found a dementia prevalence of 10.6% (5), much higher than the 7% estimate for Southeast Asia (2), and 23.2% had mild cognitive impairment (MCI). Almost half (48.1%) of those with baseline MCI status, from the same cohort, developed incident dementia after 3–4 years of follow-up (6) indicating MCI as a potentially progressive condition that makes older individuals at high risk for developing dementia (7). Progression from MCI to dementia occurs at a higher rate with an estimated conversion rate of 10–15% per year (7, 8). The odds of progressing to dementia is increased by 3.07 times among those with MCI (6) and further increased by 1.53–2.95 times higher if identified with comorbid conditions such as cardiovascular risks and metabolic syndrome (9). This condition is prevalent in Filipino older adults, with around 82.0% of men and 70.4% of women having at least one cardiovascular risk factor (hypertension, diabetes, dyslipidemia, and smoking) (5). Mixed pathologies and comorbidities are common in the MCI population; therefore, multicomponent treatment strategy is a reasonable approach (7, 10).

Addressing several modifiable risks factors potentially accounts for 40% case preventions or delays in dementia incidence, acknowledging that cognitive decline is a multifactorial phenomenon (11). Complex interventions that address multiple risk factors are limited, but demonstrated promising results (12, 13). One randomized controlled trial (RCT) assessing the efficacy of multicomponent intervention combining exercise, cognitive training, and management of cardiovascular risk factors, the Finnish Geriatric Intervention Study to Prevent Cognitive Impairment and Disability (FINGER), demonstrated cognitive benefits at a 2-year interim endpoint (12). The study population were older individuals with high vascular risk scores and cognitive performance slightly lower than population norms (14). Another RCT of a 6-year multidomain vascular care intervention, although it did not reduce the incidence of all-cause dementia, showed potential benefits particularly among participants with high adherence rate and baseline untreated hypertension (13). Two significant insights can be drawn from these studies (12, 13): first is selection of high-risk population who could benefit more from the intervention, and second, combination of physical activity and vascular risk management can provide more cognitive benefits than interventions targeting vascular risks alone, hence, the rationale for designing a multicomponent intervention combining physical activity such as dance (INDAK—Improving Neurocognition through Dance and Kinesthetics) (15), with intensive vascular risk management and monitoring of adherence, and nutrition counseling.

Physical activity has been shown to improve cardiovascular fitness and cognitive function across various domains (16). While dancing seems primarily a physical activity, it offers a complex and enriched environment for older adults (17) by providing increased multisensory and motor stimulations, challenging cognitive tasks, and increased social interaction (15, 17). Promisingly, a well-designed RCT demonstrated through structural magnetic resonance imaging (MRI) that dancing has superior positive long-term effects on neuroplasticity compared with repetitive or routine exercise. This study was conducted among cognitively healthy older adults (18–20); thus, the benefits of dance on brain and cognition for older adults with MCI remains to be studied (21). Dance is a mind and body activity, which is demonstrated to improve global cognitive and executive function (21, 22), as well as improve balance (18, 20), the major control center for which is the cerebellum. Interestingly, a ground-breaking study from Chen and Desmond (23) demonstrated by using functional MRI (fMRI) that cerebellar integrity is associated with cognitive performance highlighting the critical role of cerebellum in non-motor processes expanding the study of neuroplasticity in this area of the brain when studying dance and cognition. It has positive benefits on gross-motor coordination and balance, which can facilitate and maintain the cerebro-cerebellar functional connectivity of the brain. Specifically, Chen and Desmond (23) examined the higher cognitive function of verbal working memory and identified specific regions [inferior frontal gyrus (IFG), the inferior parietal lobule (IPL), and the right superior and inferior cerebellum] to be functionally connected in this network. For visual working memory, Ng et al. (24) found the bilateral dorsal lateral prefrontal cortex (DLPFC), bilateral IPL, and bilateral superior and inferior cerebellum (more so on the left) to be activated. This improved connectivity is hypothesized to improve cerebellar and hippocampal function particularly on working memory, which is a component of executive functions (EFs). We define the core EFs to constitute inhibition, interference control, working memory, and cognitive flexibility (25). A brief battery for executive function composite (EFC) scales and the Mnemonic Similarity Task (MST) (26, 27) will be used to evaluate cognitive changes due to dancing. In order to capture the neuroplasticity of the cerebro-cerebellar networks, we will apply a well-validated, robust visual working memory fMRI task (24). As verbal working memory required the reading of alphabets, we decided to use the visual working memory task instead as it is non-language dependent and has been well-validated in previous studies (24, 28). Although a few studies that analyzed the effect of dance using fMRI have demonstrated enhancement of cortical and subcortical functional connectivity (29–31), these studies were mostly cross-sectional in design, involving young participants. Furthermore, benefits of dance extend beyond neurocognitive benefits by improving physical, functional, socioemotional, and quality of life in older adults (22).

In addition, changes in white matter integrity as measured by diffusion tensor imaging (DTI), intrinsic functional connectivity examined with resting-state fMRI, and brain volume changes examined by voxel-based morphometry (VBM) have been found to be enhanced with physical activities such as dancing in older adults (18–20, 30, 31). We will evaluate how these brain changes are associated with the cognitive measures to understand the effect of dancing on other EFs and memory encoding in our MCI sample.

This study aims to evaluate a community-based intervention program focusing on the effect of dance with intensive management of vascular risks to maintain cognitive performance among older persons with MCI. It further attempts to document its potential underlying neural mechanism through structural and functional MRI. We hypothesize that the intervention group will primarily have better cognitive function and potentially improve functional balance, mood, and quality of life than controls. For task-fMRI, we hypothesize that the functional connectivity of the targeted cerebro-cerebellar networks (DLPFC—superior cerebellum and IPL—inferior cerebellum) involved in visual working memory will be enhanced in the intervention group compared with controls. For resting-state fMRI, we will examine changes in the default mode network, executive control network, and salience network in the intervention group compared with the control group. We expect to see enhanced white matter integrity (examined by diffusion MRI) in related networks in the intervention group compared with the control group. We also hypothesize brain volume increases in frontal brain regions in the intervention group relative to the control group.

## Methods and Analysis

### Study Design

FINOMAIN is a community-based, single-blind (outcome assessor), cluster-randomized controlled trial of a multicomponent intervention with two arms: an intervention and a control arm. The intervention arm will receive 12 months (1 h, twice per week) of dance training called INDAK, and intensive vascular risk management, which includes regular visits with the study physician for treatment and monitoring of vascular risks and nutrition counseling. A waitlisted control group will receive usual vascular care that includes general advice on management of risks and referral to the local health clinic. The protocol was prepared based on SPIRIT (Standard Protocol Items: Recommendations for Interventional Trials) guidelines (32), and the multicomponent intervention design followed the Medical Research Guidelines on the evaluation and development of complex interventions (33). A pilot trial will be carried out to assess the acceptability, safety, and feasibility of this multicomponent intervention. Ethics approval has been granted by St. Luke's—Institutional Ethics Review Committee (CT-18146) and was retrospectively registered at Clinicaltrials.gov with identifier NCT04301544 (trial registration data available at: https://clinicaltrials.gov/ct2/show/NCT04301544).

### Study Population

Participants are community-dwelling Filipinos aged 60 years old and above, with MCI.

#### Inclusion Criteria

MCI evaluation is based on Petersen criteria (34), i.e., cognitive symptoms documented by standardized cognitive test ≥ 1.5 standard deviation (SD) below Filipino norms for Alzheimer Disease Assessment Scale—Cognitive (ADAS – Cog) (35) but do not fulfill DSM-5 criteria for major cognitive disorders (36) and has a Clinical Dementia Rating (CDR) of 0.5 (37).No significant functional impairment based on the Lawton's Instrumental Activities of Daily Living (IADL) scale (38) quantified as no more than 10 points (15).No significant neuropsychiatric symptoms as detected by the Neuropsychiatric Inventory— Questionnaire (NPI-Q) (39) quantified as no more than six points (15).Able to read and write to complete assessment.Able to provide written consent and willingness to comply with study visits/testing over the 12-month intervention and assessment period.

#### Exclusion Criteria

Major sensory problems such as hearing and visual impairment that limits testing or dance participation.Any preexisting illness that in the judgment of the study physician precludes engagement in moderate physical activity.Intake of any anticholinergic drugs or cognitive-impairing/-enhancing medications.

### Sample Size Determination

Sample size was calculated based on the results of quasi-experimental study for INDAK where we compared the mean difference in ADAS-Cog, the primary outcome, from baseline and after 1-year follow-up between intervention and control groups. In that study, ADAS-Cog decreased by 3.16 (SD = 5.97) in the intervention group and 0.91 (SD = 8.69) in the control group (15), with an α error of 5% and β of 5% (power of 95%), and a one-tailed alternating hypothesis in favor of the intervention group, the sample size calculated is 136 per group or 272 for two groups (intervention and control). To account for clustering, a design effect of two will be adopted. This means that the total sample will be 544, with 272 participants per group. Allowing for 10% dropout, the final total sample size required in this study is 605 participants. This will be divided into 20–25 clusters per treatment arm. One cluster will have 12–15 participants, a range we found to be optimum for the intervention in the previous observational study. For MRI, at least 20% of the sample will undergo MRI, selected randomly from both intervention and control arm. This will be proportionally allocated to both arms. The estimated pilot size is 60 participants or 30 per group, expecting higher dropouts; 20% allowance was added giving a final pilot size of at least 72 or 36 per group. The pilot phase is to assess the acceptability of combined interventions (i.e., INDAK, vascular risk management, and nutrition counseling), determine adherence and dropout rates, as well as identify challenges and feasibility of conducting and advancing our research findings with neuroimaging outcomes.

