### Outcome Measures

#### Primary Outcome Measures

Alzheimer's Disease Assessment Scale—Cognitive (ADAS-Cog) (42): This test consists of 11 tasks measuring the core cognitive deficits of Alzheimer's disease (AD), such as disturbances of memory, language, praxis, attention, visuospatial function, and other cognitive abilities. The ADAS-Cog was validated for use in the Filipino elderly with age- and education-stratified norms (35, 42). Its psychometric properties have good reliability (e.g., Cronbach's α 0.84; test–retest intraclass correlations/ICC: 0.93) and validity (MMSE-P: −0.88 and CDR: 0.81) (42, 43). Score ranges from 0 to 70 points, with lower scores indicating better cognitive function.Mnemonic Similarity Task (MST) (27): This task places strong demands on pattern separation, memory representation, and cognitive domains highly correlated with hippocampal function. It consists of two phases: encoding and test part. The encoding phase presents 128 colored photographs of objects on a computer screen to be classified by participants as either indoor or outdoor objects. The test phase consists of 192 items (64 targets, lures, and foil items each), in which participants engaged in a modified recognition task identifying each item as old, similar, or new items based on the encoding phase. Percentage accuracy is calculated, with higher percentage indicating better function. MST has been used in identifying hippocampal dysfunction associated with aging and dementia and found to be a sensitive and reliable tool in tracking the progression of cognitive decline and treatment efficacy (26, 27).Executive function composite (EFC) scales: This combines measures for verbal fluency task, which evaluates language and executive ability for categorical tasks (44); number cancellation task, which assesses visual modality and selective attention (45); and digit symbol substitution task (46) and trail making task (part B) (47), both of which examines visual scanning, executive function, processing, and psychomotor speed. Higher composite scores indicate better executive function. Each neuropsychological test demonstrate good validity and reliability to assess for executive function and track cognitive decline in older adults, for further details see references (48, 49).

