### Randomization and Allocation Concealment

Cluster randomization will be used to ensure blinding and avoid contamination of group allocation (33), which was one of the challenges in the quasi-experimental study for INDAK (15). The rationale behind this design is to ensure sociocultural fitness of study to the close-knit and socially collective nature of the Filipino community. Communities are “*barangays*,” the smallest government unit in the Philippines, which is mostly characterized by a high population density (1). People live close to each other, acquainted and frequently interact with one another. They share the same public space and health services (e.g., health center, social center), therefore individual randomization within the same community will limit opportunity of concealing treatment allocation. A barangay is referred to as one cluster in this study.

Randomization will be done after baseline assessment is completed (V1); hence, allocation is concealed to the assessors. Clusters will be randomized to a 1:1 ratio by the study statistician using a computer-generated randomization method, constrained using minimization. That is, each community will be allocated with a probability of 0.8 to the group that minimizes the imbalance at baseline of the means of the primary outcomes. The study statistician will inform the primary investigator of group allocation, and the study coordinator will arrange the delivery of intervention. The outcome assessors will be blinded to group allocation. Their engagement with the participants will be limited only to the day of assessment.

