#### Data Management and Statistical Analysis

Data will be encoded independently by two research associates, and inconsistencies will be double checked with the data source to ensure data accuracy. All tests (primary and secondary outcomes) will be analyzed as independent continuous measures; additionally, we will also analyze for executive function composite (EFC) score derived by dividing independent test scores with their maximum possible scores and summing across tests for EFC, as was done in previous studies (63–65).

The study will employ univariate, bivariate, and multivariate statistics. For univariate, descriptive statistics (mean/SD; frequencies/percentages) will be used to summarize sociodemographic and other baseline characteristics. The bivariate analyses that examine underlying relationships between the outcomes and other clinical characteristics are the following: independent *t*-test for continuous variables and Chi square test (or Fisher exact test when ≤ 20 of the cells have the expected count <5) for categorical variables to compare baseline data between the intervention and control groups. Pairwise comparison of the randomization groups per timepoint will also be done to explore differences at different times using independent *t*-test. For multivariate analyses, the study would estimate the effect from baseline to follow-up at 12 months between randomization groups. Since the participants will be assessed three times (at baseline, 6th and 12th months), the study will be using multilevel mixed models to test the significance between group means but controlling for possible confounders (i.e., when age, sex, and education were not successfully controlled for in the randomization design). Necessary diagnostics will also be considered. This multilevel model is appropriate as it can take into account the clustering effect, and the number of clusters in this study is moderately sized (25–30 clusters per arm).

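### The trial is sized on ADAS-Cog alone at one-sided 5%, but three outcomes are named primary and analysed separately, so neither the 5% error rate nor the power is secured for the primary claim

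*Protocol article*

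**What the plan says.** The protocol article describes the primary outcome in five places.

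- **Sample Size Determination** takes its inputs from the quasi-experimental INDAK study, where "we compared the mean difference in ADAS-Cog, the primary outcome, from baseline and after 1-year follow-up between intervention and control groups". The inputs are "ADAS-Cog decreased by 3.16 (SD = 5.97) in the intervention group and 0.91 (SD = 8.69) in the control group", and the test is "a one-tailed alternating hypothesis in favor of the intervention group" at 5%, with a stated power of 95%. The result is 136 per group, then 272 per group after a design effect of two, then 605 in total after 10% dropout. No effect size or power is given for any other outcome.
- **Abstract**: "The primary outcome is cognitive performance assessed by the Alzheimer's Disease Assessment Scale—Cognitive (ADAS-Cog), Mnemonic Similarity Tasks (MST), and executive function composite (EFC".
- **Outcome Measures**: under the plural heading "Primary Outcome Measures", ADAS-Cog, MST and EFC are listed one after another with no ranking.
- **Randomization and Allocation Concealment**: each cluster is allocated, with probability 0.8, to "the group that minimizes the imbalance at baseline of the means of the primary outcomes". The plural appears again.
- **Data Management and Statistical Analysis**: "All tests (primary and secondary outcomes) will be analyzed as independent continuous measures", with the EFC composite score analysed in addition.

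None of these sections ranks the three outcomes, divides alpha between them, or says whether one or all must succeed.

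**The concern.** A trial sized on one endpoint at one 5% level supports one confirmatory test. Here the sizing section supplies that for ADAS-Cog, while the rest of the document gives MST and EFC the same primary standing. The stated hypothesis is simply better cognitive function in the intervention group, so a favourable MST result beside a null ADAS-Cog result could be presented as confirmation, or equally as failure. The document does not settle which. At stake are the false-positive rate of the main claim, the power behind it, and the reading of discordant results.

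**Working it through.** **1. Reproduce the sizing figure.** Inputs, all from Sample Size Determination: difference 3.16 − 0.91 = 2.25; SDs 5.97 and 8.69; one-sided alpha 0.05.

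n per group = (z₁₋α + z_power)² × (SD₁² + SD₂²) / difference²

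SD₁² + SD₂² = 35.64 + 75.52 = 111.16, and 111.16 / 2.25² = 21.96.

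- At 80% power: (1.645 + 0.842)² × 21.96 ≈ 136.
- At 95% power: (1.645 + 1.645)² × 21.96 ≈ 238.

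The stated 136 therefore matches 80% power, not the stated 95%. Power at 136 is 80.1%. That is a separate defect, and it is why 80% is the working value below. The later steps reproduce: 136 × 2 = 272 per group, 544 in total, and 544 / 0.9 = 604.4, rounded up to 605. Because the design effect of two is built in, 272 enrolled per group carries the information of 136 independent participants.

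**2. Three primaries, success on any one.** Each is assumed to be tested at the sizing section's one-sided 5%. Under independence, 1 − 0.95³ = 14.3%. With a common correlation ρ, the error is 1 − Φ₃(1.645, 1.645, 1.645; ρ), where Φ₃ is the trivariate normal distribution function.

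**3. Three primaries, all must succeed.** Error is at or below 5%. If each has 80% power, joint power is Φ₃(0.842, 0.842, 0.842; ρ), which is 0.8³ = 51.2% under independence.

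| Assumed ρ | Error, any one succeeds | Joint power, all three succeed |
|---|---|---|
| 0 | 14.3% | 51% |
| 0.3 | 13.0% | 57% |
| 0.5 | 11.8% | 61% |
| 0.7 | 10.3% | 66% |
| 0.9 | 8.0% | 72% |

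The document gives no correlations, so every ρ here is an assumption. If each outcome really had the stated 95% power, joint power would be 86% to 92% over the same range, but 136 per group does not deliver 95% even for ADAS-Cog.

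**4. Alpha split three ways.** Each test is at 0.05 / 3 = 0.0167, critical value 2.128. At 136 per group the standardised effect is 2.25 / √(111.16 / 136) = 2.489. Power = Φ(2.489 − 2.128) = Φ(0.361) ≈ 64%.

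**5. One primary, ADAS-Cog.** Error is 5% one-sided and power is 80.1%. This is the only reading under which the calculation describes the primary test.

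**The case against.** The strongest reply has three parts.

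First, a rule for combining several primary measures is commonly left to the statistical analysis plan, which is not shown, and a journal article condenses further. That stands: the absence of a multiplicity rule is not a finding in itself. What remains is stated text. How many outcomes are primary, and which of them the sample size serves, are both written in this document and do not match. A later plan would have to override one section or another.

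Second, the words calling ADAS-Cog the primary outcome occur in a sentence about the quasi-experimental study and may describe only that study. This is a fair reading, and sizing on the one measure with prior data is not in itself a contradiction. Even so, the sizing covers one outcome while three are primary.

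Third, a reader might infer that the 5% error rate definitely fails. The document does not support that. The rate is exceeded only if a win on any one outcome counts, and no section says so. If all three must succeed, or if ADAS-Cog leads, error stays within 5%.

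A reader might also count seven primary tests by adding the four EFC component tests. The analysis section does have the tests analysed separately, but the outcome section lists those four only as ingredients of one primary measure. Separate analysis does not give them primary status, so only the three-outcome figures apply.

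**Conclusion.** The concern holds in a limited form: the 5% error rate and the power are not secured, which is different from saying they are lost. If any one success suffices, error is about 8% to 14%. If all three are required, joint power is about 51% to 72%. Under an equal alpha split, ADAS-Cog power is about 64%. No reading with three primaries is supported by the calculation as written.

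These figures rest on the following assumptions: one-sided 5% for each outcome, carried over from the sizing section because the analysis section states no level; a common correlation between 0 and 0.9; 80% power for MST and EFC, for which the document gives no effect size; and the design effect of two taken as stated.

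**What to change.** Before the full study starts:

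- Name ADAS-Cog at 12 months as the single primary outcome, matching the sample size.
- Make MST and the EFC composite key secondary outcomes, tested in a fixed order (or by Holm between the two) only if ADAS-Cog is significant. Label the individual EFC components exploratory.
- Align the Abstract, Sample Size Determination, Primary Outcome Measures, and Data Management and Statistical Analysis.
- In Randomization and Allocation Concealment, list by name the measures that the minimization continues to use. Eight clusters (72 participants) have already been randomized under a rule that refers to the primary outcomes in the plural, so a change of label must not silently change the algorithm.

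If the sponsor prefers three primaries, state the any, all or alpha-split rule and restate the power under it. As a guide, using ADAS-Cog inputs only, an equal split needs 194 per group for 80% power: 194 × 4 = 776 after the design effect, and 776 / 0.9 gives 863 after dropout. At the stated 95% power it needs 313 per group, hence 1,252 and then 1,392.

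The single-primary option costs only protocol wording and no extra participants or data. Its small downside is that MST and EFC lose stand-alone primary status.

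### On the plan's own inputs, 136 per group (605 enrolled) gives 80% power, not the stated 95%, which would need 238 per group

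*Protocol article*

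**What the plan says.** All the sizing inputs are in one paragraph of the protocol article, under Sample Size Determination.

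- **Effect and spread**, from the earlier quasi-experimental study: "ADAS-Cog decreased by 3.16 (SD = 5.97) in the intervention group and 0.91 (SD = 8.69) in the control group".
- **Error rates:** "with an α error of 5% and β of 5% (power of 95"%), with "a one-tailed alternating hypothesis in favor of the intervention group".
- **Result**, tied directly to that power: "power of 95%), and a one-tailed alternating hypothesis in favor of the intervention group, the sample size calculated is 136 per group", which is 272 in total.
- **Clustering:** "To account for clustering, a design effect of two will be adopted", which brings the total to 544. A 10% dropout allowance then gives 605.
- **Clusters:** "This will be divided into 20–25 clusters per treatment arm", at 12–15 participants each. The Abstract gives the same 20–25 per arm.

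The section on Recruitment and Assessment Visits takes 605 as the enrolment target and rests it on this calculation. The Data Management and Statistical Analysis section supports its multilevel model with a different count: "the number of clusters in this study is moderately sized (25–30 clusters per arm").

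**The concern.** The paragraph gives every input a reader needs to repeat the calculation, and the result does not follow from them. A standardised effect of about 0.30 with 136 per group cannot deliver 95% power at one-sided 5%.

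Power is the main design property that the sample size is meant to secure. As written, ethics reviewers, funders and later readers are told that the trial has a 5% chance of missing its assumed effect. If the true figure is about 20%, a non-significant result could be taken as much stronger evidence against the intervention than it is.

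The cluster count is a second, smaller inconsistency. The analysis section relies on having a moderate number of clusters, but the number it gives is not the one the sample size provides.

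**Working it through.** **Inputs** (all from Sample Size Determination)

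- Difference in mean change: 3.16 − 0.91 = 2.25, squared 5.0625
- Sum of variances: 5.97² + 8.69² = 35.64 + 75.52 = 111.16
- Root-mean-square SD: √(111.16/2) = 7.455, so the standardised effect is 2.25/7.455 = 0.302
- One-sided alpha 5%: z = 1.645

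**Formula** (two independent means, 1:1 allocation)

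n per group = (z_alpha + z_beta)² × (SD₁² + SD₂²) / difference²

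**Reproducing the plan's figure**

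| Power | Calculation | n per group |
|---|---|---|
| 80% | (1.645 + 0.842)² × 111.16 / 5.0625 | 135.75, so 136 |
| 90% | same formula | 188.0 (189 after rounding up) |
| 95% (as stated) | (1.645 + 1.645)² × 111.16 / 5.0625 | 237.6, so 238 |

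The stated 136 appears at 80% power. The stated 95% needs 75% more (238/136 = 1.75). The noncentral t distribution gives 137 and 239, so the choice of approximation does not explain the gap.

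**Other routes to 136 at 95% power**

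- One-sided with a single SD: 153 (SD 5.97), 230 (mean of the two SDs) or 323 (SD 8.69).
- Two-sided: 183 to 388, depending on the SD.
- One-sample formulas with SD 7.455: 119 one-sided or 143 two-sided.
- Solving for the common SD that would give 136 returns about 5.64, below both stated SDs.

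None reproduces the plan's figure.

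**Later steps**

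- 136 × 2 = 272 in total; × 2 for the design effect = 544; 544/0.9 = 604.4, so 605. These are correct.
- Working back: 605 × 0.9 / 4 = 136.1 effective participants per arm, so the enrolled sample has the same power as the unadjusted 136.

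**Power at 136 effective per arm**

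- One-sided 5%: 80.1% (normal), 79.9% (noncentral t), about 79% with a t reference on 38–48 cluster degrees of freedom.
- Two-sided 5%: 70.2%.
- Difference detectable with 95% power, one-sided: (1.645 + 1.645) × √(111.16/136) = 2.97 points, against the assumed 2.25.

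**Size needed for 95% power**

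238 × 2 groups = 476; × 2 for the design effect = 952; 952/0.9 = 1,057.8, so 1,058.

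**Cluster count**

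- 605/15 = 40.3 and 605/12 = 50.4 clusters, about 20–25 per arm. This agrees with Sample Size Determination and the Abstract.
- 25–30 per arm means 50–60 clusters, which at 12–15 each is 600–900 people. The two ranges meet only at 25 per arm.

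**The case against.** The mismatch itself is hard to dispute, because the 5% beta and 95% power agree with each other in the text and the inputs are explicit. The case on the other side concerns how far the conclusion reaches.

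- **Which figure is the slip?** The document does not say whether the power or the sample size is wrong. The exact match at 80% makes a misreported beta likely, but that is inference. This stands, and the fix gives both routes.
- **The 80% is conditional.** It accepts the design effect of 2, for which no intracluster correlation is given. At 12–15 per cluster, a design effect of 2 implies a correlation of about 0.07–0.09 (1/14 to 1/11). If the correlation were 0.02–0.05, an assumption not found in the document, 605 enrolled would give about 85–94% power. At 0.09 with 15 per cluster it would be about 76%. The planned three-timepoint multilevel model also differs from the two-sample comparison used for sizing. This stands as a condition. It does not rescue the stated figure, which is claimed on the plan's own inputs.
- **The risk of over-reading a null result is limited.** The analysis section says confidence intervals will be examined and very wide ones treated as a sign of low power. That tempers the harm but leaves the power statement wrong.
- **The cluster ranges touch at 25, and cluster sizes may differ in practice.** Study Status reports eight clusters with 72 participants, or 9 each. At that size 605 people would need about 67 clusters. This is a reason for the sponsor to check the planned cluster size. It does not support 25–30, since the document's own 12–15 per cluster gives 20–25.
- **Two-sided power is outside the error,** because the plan openly states a one-tailed hypothesis. This is fair, and that figure is optional.

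**Conclusion.** The concern holds. With the stated difference, SDs and one-sided 5% alpha, 136 per group gives 80.1% power, and 95% requires 238. The type II error is about 20% against a stated 5%, and the shortfall passes unchanged into the target of 605. This rests on the two-mean comparison the plan itself used, its design effect of 2 and its 10% dropout. A different true intracluster correlation would move the achieved power, but would not make 136 the answer to the calculation as described.

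The analysis section's 25–30 clusters per arm is also inconsistent with the 20–25 that the Abstract and sample size section give and that 605 at 12–15 per cluster supports. Because the false statement concerns the trial's headline power, it should be corrected before the full study resumes.

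**What to change.** 1. In Sample Size Determination, keep 605 and state the power as 80% (beta 20%) at one-sided alpha 5%, on the assumed design effect of 2. Giving the two-sided 5% power (70%) beside it would help readers but is optional.
2. In Data Management and Statistical Analysis, change the cluster count to 20–25 per arm, so that the support for the multilevel model matches the sample size.
3. The sponsor should confirm that 80% was the intended power. If 95% was intended, the sample size must change instead: 238 per group, 952 after the design effect and 1,058 with 10% dropout.

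Steps 1 and 2 cost only wording and need no extra participants, though the stated power becomes less favourable. The alternative in step 3 would add 1,058 − 605 = 453 participants. Study Status describes recruitment as stopped after eight clusters, so either correction can be made before the main phase begins.
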